### Primary outcome measures

The first primary outcome measure will be *societal participation in the past 6 months*. This is expressed in paid work, voluntary work and schooling (yes/no). This measure will be derived from the subscale Employment/Occupation of the self-report Birchwood Social Functioning Scale (SFS) [44] using a hierarchical index to dichotomise whether or not there is an increase in societal participation at 6 and/or 12 months. The SFS was constructed to measure areas of functioning that are crucial for the community maintenance of people with schizophrenia (i.e. psychosocial functioning). The SFS focuses on fundamental characteristics of societal functioning and consists of seven subscales:

1) Social engagement/withdrawal, 2) Interpersonal behaviour, 3) Pro-social activities, 4) Recreation, 5) Independence-competence, 6) Independence-performance, 7) Employment/occupation.

The SFS proved a reliable and valid instrument for measuring psychosocial functioning with a high level of internal consistency (Full scale α = 0, 80, Factor loadings >0, 70).2.The second primary outcome is *current level of societal participation,* which will be measured using the Dutch National Societal Participation Ladder [45]. The Dutch National Societal Participation Ladder was developed for the Social Support Act (Dutch: WMO) and establishes the level of societal participation in six steps:

1 = severe social isolation, 2 = social contacts outside the home, 3 = participation in organised activities, 4 = having an unpaid job, 5 = having a paid job with support, 6 = having a paid job.

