
### Sample size

With regard to the main outcome measure, the power analysis was based on the earlier finding that the proportion of patients engaged in meaningful activities increased by 11.5 % for BPR compared to 0 % for CAU after 1 year [9]. With this expected difference in proportion of change in both conditions, the study will have a power of 80 % (alpha = 0.05, two sided) if complete data from 2 × 90 patients is obtained. Furthermore, with regard to the economic evaluation, SF-12D is used to calculate a preference-based utility index, SF-6D. In the preceding RCT, the SF-12D [58] was not used, but scores on the WHOQOL are available [74]. For patients with rehabilitation goals in the area of societal participation, the differences between BPR and CAU after one year were 1.23 (SD 2.18). Calculating the required power of the study with this parameter, only 60 patients in each condition are needed to achieve 80 % power. Power rises to 95 % with 90 participants in each condition, which is needed for the primary outcome measure. Taking into account an average dropout rate of 20 % and a maximum dropout rate of 25 % after one year follow up, at least 225 respondents with SMI are needed for this trial. The number of patients eligible but not willing to participate will be carefully monitored to support the BIA. A pilot will be conducted for the additional 25 patients with severe and persistent eating disorders who will also participate in this study, since no information is available on the differences in change that can be expected after a year with and without BPR support for this group.

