### Randomisation

After written informed consent has been received, an independent investigator using a stratified block randomisation scheme will assign participants to CAU or BPR. Stratification factors are ‘centre’ and ‘employment in the preceding year (yes/no)’. The group with eating disorders has an additional stratification factor: ‘duration of hospitalisation in the 6 months prior to inclusion (less/more than 3 months)’ because this group in particular needs support with rehabilitation goals directly after hospitalisation. In order to avoid large differences between both conditions in the level of costs during the period before commencement of the study, duration of hospitalisation will be added as an extra stratification factor for this group. Random allocation to either experimental group or control group will take place immediately after the baseline measurements have been completed.

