To analyse results on the main outcome, the difference in percentage of patients with increased participation in both groups after 1 year will be compared. Firstly, descriptive statistics will be performed with regard to the proportions of patients with increased participation. Secondly, risk differences yielding numbers needed to treat (NNT) will be calculated using (multilevel) regression models to be adjusted for research centre and employment in the year preceding the study. Other possible confounders such as sociodemographics, psychiatric symptoms and remission, quality of the therapeutic relationship or educational level of MH professional will be added if comparison between intervention group and control group shows differences between these groups despite randomisation. In addition, sensitivity analyses will be performed on all outcomes, including only respondents who participated in at least two contacts with the rehabilitation worker and excluding patients for whom the outcome was rated indirectly because they were not available for interviews at 6 and 12 months. Secondary outcomes are (I) continuous variables indexing quality of life, psychosocial functioning, recovery and self-efficacy and (II) binary variables indexing patients’ experience of success in achieving their rehabilitation goals (yes/no). Patients’ experience of success in achieving their rehabilitation goals could also be presented as an (III) ordinal variable (yes/no/partially). Means and proportions of these variables at baseline, 6 and 12 months will be modelled using both multilevel linear and logistic regression analyses in which each person (level 2) contributes three observations (level 1), making adjustments for participating centre, and other confounders. Treatment effects will be quantified using the Time (baseline, 6 and 12 months) × Group (BPR and CAU) interaction, assessing whether change in the outcome of interest over time differs significantly between the two groups. Effects of time stratified by treatment group will be calculated by linear combination of the appropriate terms in the model using the General Linear Model (GLM) procedure in SPSS.

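### The primary model leaves the baseline level of the participation index to a check for observed imbalance, although the outcome is an increase from that level; the cost is modest precision, not bias

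*Protocol article*

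**What the plan says.** In the protocol article, Primary outcome measures, the first outcome covers paid work, voluntary work and schooling over the past six months. It is scored from the SFS Employment/Occupation subscale "using a hierarchical index to dichotomise whether or not there is an increase in societal participation at 6 and/or 12 months".

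Under Primary clinical analyses, "the difference in percentage of patients with increased participation in both groups after 1 year will be compared". Risk differences and NNTs come from "regression models to be adjusted for research centre and employment in the year preceding the study". These two covariates are also the stratification factors under Randomisation, where employment is a yes/no item. The article then lists "Other possible confounders such as sociodemographics, psychiatric symptoms and remission, quality of the therapeutic relationship or educational level of MH professional", which "will be added if comparison between intervention group and control group shows differences between these groups despite randomisation". The list is open, the baseline index is not named in it, and no size or test of difference is given as the trigger.

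Randomisation also states that allocation follows immediately once the baseline measurements are complete.

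**The concern.** An increase is counted from the patient's own starting point, so the starting point is directly prognostic: a patient with no activity can rise several steps, and one at the top cannot rise at all. The stratum variable does not carry all of this. It is binary, looks back twelve months rather than six, and is worded as employment. On that wording, a volunteer or a student without a job falls in the same stratum as someone with no activity.

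Two things are at stake. First, prognostic information already held for every patient is not used by rule, so the risk difference is less precise than it could be. Second, whether it is used depends on an imbalance check with no stated threshold, so the headline model is not fully fixed in advance. The same outcome supplies the effect side of the cost-effectiveness ratio.

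**Working it through.** **Inputs from the article.** 90 patients per arm with complete data (Sample size). The planned effect, where "the proportion of patients engaged in meaningful activities increased by 11.5 % for BPR compared to 0 % for CAU after 1 year", gives a risk difference of 0.115 and NNT = 1/0.115 = 8.7. The article states no baseline distribution of the index and no chance of increase by level, so there is no plan figure to reproduce. Everything below rests on assumed ranges.

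**Step 1: size of chance imbalance.** Let p be the share of patients at a high starting level. Under simple randomisation the SD of the difference between arms is √(2p(1−p)/90).
- p = 0.20: √(0.32/90) = 0.060
- p = 0.50: √(0.50/90) = 0.075

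Simulated stratification on prior-year employment, with p = 0.20 to 0.40 and 30% to 70% of high-level patients employed in the preceding year, leaves an SD of about 4.3 to 6.9 points. The stratum helps but does not remove the imbalance.

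**Step 2: effect on the risk difference.** Shift = imbalance × difference in chance of increase between low and high starters. At 1.96 SD under simple randomisation:
- smallest: 1.96 × 0.060 × 0.10 = 1.2 points
- largest: 1.96 × 0.075 × 0.30 = 4.4 points

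**Step 3: first set of simulations.** 20,000 trials per scenario, 90 per arm, 1:1 within employment strata. Assumed mix: 50–64% no activity, 20–34% voluntary work or schooling, 16–18% paid work. The chance of increase falls with level; the true risk difference is 11.4 to 12.1 points.

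| Scenario | SD without baseline level | SD with it | Ratio squared |
|---|---|---|---|
| 1 | 0.0525 | 0.0519 | 1.023 |
| 2 | 0.0541 | 0.0521 | 1.078 |
| 3 | 0.0499 | 0.0498 | 1.004 |

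The gain is about 0.5% to 8% in equivalent sample size. The slope of the estimate on imbalance in the no-activity share is 0.10 to 0.23 without the covariate and about 0 with it. That imbalance has a 95% limit of about 12 to 13.5 points, so the shift there is 0.10 × 12 = 1.2 to 0.23 × 13.5 = 3.1 points. In the strongest case an NNT of 1/0.114 = 8.8 moves to 1/0.145 = 6.9 or 1/0.083 = 12.

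**Step 4: second set of simulations.** 4,000 trials per scenario, 90 per arm, stratified by prior-year employment. Assumed: 20–40% at a high level with a 2% chance of increase; 10–30% chance under care as usual at a low level; true risk difference 0 or 0.115.
- The mean estimate is the same in both models: about 0 when there is no effect, about 0.115 when there is.
- Two-sided type I error is about 5–6% in both.
- With an effect present, adding the baseline level lowers the SD by about 1–8% and raises power by about 1–8 points. In the weakest case shown, (0.0603/0.0597)² ≈ 1.02; in the strongest, (0.0626/0.0576)² = 1.18. That is 2% to 18% in equivalent sample size.
- In 95% of trials the two estimates differ by at most 1.4 to 5.1 points, depending on scenario. For scale, a 2-point shift moves the NNT from 8.7 to 1/0.135 = 7.4 or 1/0.095 = 10.5.

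**The case against.** The strongest reply is that the article already covers the harmful case. Its list of further confounders is introduced as examples, so baseline participation could enter when the arms differ, and a 12-point difference is the sort the clause has in mind. This stands against any reading that the plan never adjusts for baseline participation. It does not settle the point, because the clause neither names the index nor says what counts as a difference, and a prognostic covariate improves precision even when the arms happen to be balanced.

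A reader might also infer that the primary estimate is biased or its test invalid. The documents do not support that. Under stratified randomisation chance imbalance averages zero and is already in the standard error; Step 4 shows the same mean and type I error either way. The 1.2 to 3.1 point shift is about 0.2 to 0.6 of a standard error (1.2/5.25 and 3.1/5.41). Around an estimate of 0.114, an SD of 0.0525 gives 0.114 ± 0.103, or 0.011 to 0.217, and an SD of 0.0519 hardly changes that.

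Two further objections stand in part. Both sets of simulations stratify on employment only, whereas the trial also stratifies and adjusts for centre; if participation differs by centre, the gain is smaller. And covariate detail often belongs in an analysis plan, which is not shown. Here, though, the article itself fixes the covariates and the rule for adding others, so the point concerns a stated choice.

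**Conclusion.** The point holds as a matter of efficiency and prespecification. The article fixes centre and prior-year employment and leaves the baseline level of the outcome's own index to an imbalance check without a threshold. Leaving it out costs about 0.5% to 8% in equivalent sample size under the first set of assumptions and 2% to 18% under the wider second set, whose upper end needs 40% of patients at a high level, a steep gradient in the chance of increase and a weak link to prior employment. At a 95%-limit imbalance the first set gives a shift of about 1 to 3 points.

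These sizes depend on assumed baseline mixes and on leaving centre out. The imbalance-triggered rule was not itself simulated, so nothing is claimed about its error rates; the objection to it is that it leaves the primary model open. It is tempting to extend the point to the participation ladder and total hours, but the article does not describe the models for those outcomes, so it supports no finding there.

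**What to change.** In Primary clinical analyses, name the baseline level of the SFS Employment/Occupation index as a fixed covariate in the primary model, beside centre and prior-year employment, regardless of the imbalance observed. Enter it as categories, with any merging of sparse levels set in advance. Obtain the adjusted risk difference by standardisation: predict each patient's chance of increase under each condition, average over the trial sample, and take the difference; the NNT is its reciprocal.

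The cost is a sentence or two of analysis wording. The variable is collected before allocation, so no new data, visits or patients are needed.

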### Secondary outcome measures

Secondary outcome measures will be:*Patients’ psychosocial functioning from their own perspective* is measured by the Birchwood Social Functioning Scale (for psychometric information see primary outcome measures) [44].*Patients’ psychosocial functioning from the MHC team’s perspective* is measured with the Activity and Participation Scale (perspective of MH professional) [49]. The Activity and Participation Scale captures the level of participation and activity on seven dimensions:

1) Internal social integration, 2) Basal independence, 3) Use of Media, 4) Contacts with persons outside the MHC centre/living community without leaving the centre grounds.

5) Leaving the centre grounds, 6) Potential social skills, 7) Hostility to others.

The Activity and Participation Scale can be used with outpatients as well as inpatients and has good psychometric properties (α = 0.88). Factor analysis showed one factor: ‘Level of activities and participation’.3.*Patients’ subjective experience of goal attainment* (yes/no) in achieving societal participation goals in the areas addressed, such as work and schooling. For this purpose we use a structured interview devised for previous studies [9, 50, 51].4.*Quality of life* is measured by the Manchester Quality of life Schedule/MANSA [52]. The MANSA is specifically constructed to measure quality of life in patients with psychiatric problems and focuses on satisfaction with life as a whole. The MANSA has been translated into Dutch by Van Nieuwenhuizen et al. [53]. Twelve subjective items are answered on a 7-point Likert scale ranging from 1 = couldn’t be worse to 7 = couldn’t be better and four objective items are answered with yes/no. MANSA shows adequate internal consistency (α = 0.74; [41], α = 0.81; [54]) and is highly correlated with satisfaction ratings on the Lancashire Quality of Life Profile (LQLP: *r* = > 0.82; [52]).5.*Recovery* is measured with the Recovery Assessment Scale [55]. The Recovery Assessment Scale (RAS) is constructed to measure recovery from serious psychiatric illnesses. The RAS consists of a grand score and five separate factors:

1) Personal confidence and hope, 2) Willingness to ask for help, 3) Goal and success orientation, 4) Reliance on others, 5) No domination by symptoms.

RAS has 41 items and is answered on a 5-point Likert Scale ranging from 1 = strongly disagree to 7 = strongly agree. Psychometric properties have been investigated by Corrigan [55]. Cronbach’s alpha for the five factors ranges from 0.74 to 0.87. Convergent validity for the five factors ranges from moderate (R^2^ = 27.7 %) to fairly high (R^2^ = 68.9 %).6.*Self-efficacy* is measured with the General Self Efficacy Scale (GSES) [56]. This scale consists of 10 items to measure Self-efficacy on a 4-point Likert Scale ranging from 1 = not at all true to 4 = exactly true. Perceived self-efficacy is the belief in one’s competence to tackle difficult or novel tasks and to cope with adversity in specific demanding situations. The GSES has good psychometric properties: Cronbach’s alpha ranges from 0.79 to 0.90 in various study samples and self-efficacy is positively correlated with Quality of Life [57].

The following secondary outcome measures are specifically used for the cost effectiveness study.7.*Generic health status* is measured with the 12-item Short Form Health Survey (SF-12) [58]. The SF-12 is a short and efficient instrument to measure functional health and wellbeing from the patient’s point of view. In particular, the subjective evaluation of one’s physical, psychological and social functioning. It is a shortened version of the well-known SF-36 and covers the same 8 dimensions, with one or two questions per domain:

1) Physical functioning, 2) Role-Physical, 3) Bodily Pain, 4) General Health, 5) Vitality, 6) Social Functioning, 7) Role-Emotional, 8) Mental Health.

In our study, we will use the 4-week recall version. SF-12 shows good test-retest reliability with coefficients ranging from 0.76 to 0.89 [59]. Also, validity is good with Relative validity coefficients (RV) ranging from 0.63 to 0.92. Gandek et al. [60] tested the psychometric properties of SF-12 in nine European countries and found substantial correlations between the summary measures scored from SF-36 and SF-12 Health Surveys. Also, Jenkinson [61] found SF-12 to have the same capability of measuring change in health status over time as the SF-36. We will use the methodology developed by Brazier and Roberts [62] to estimate preferences for health states based on specific items (often referred to as the SF6D) from the administered SF12. These preferences will subsequently be used to derive Quality Adjusted Life-Years (QALYs), which is a commonly used outcome in economic evaluations [63].8.*Medical costs* will include costs of the interventions (BPR and CAU), inpatient and outpatient mental health care, general health care, costs of day activity institutions and medication use. Healthcare consumption will be registered with a detailed questionnaire administered to the respondents at each of the measurements. This questionnaire was adapted to the specific context of the current study, and partially based on the Tic-P by Hakkaart et al. [48]. Unit prices will largely be based on Dutch standard prices in order to facilitate comparisons with other economic evaluations [64]. Apart from medical costs, non-medical costs will be assessed as well.9.*Non-medical costs* will be assessed with the same questionnaire, especially costs of informal care and costs related to productivity losses.

### Other measures

The following measures include data on possible confounding and/or mediating variables.*Sociodemographic information* will be gathered by means of a structured interview scheme at the start of the study and checks will be performed in the interviews that follow at 6 and 12 months.*Psychiatric symptoms and remission* are measured with the Brief Psychiatric Rating Scale [65–67] in order to control for large changes in symptomatic functioning. The BPRS was developed as a quick and efficient method to describe and evaluate change in psychiatric symptoms. We use the 24-item version which measures the following symptoms: 1) Somatic concern, 2) Anxiety, 3) Depression, 4) Suicidality, 5) Guilt, 6) Hostility, 7) Elevated Mood, 8) Grandiosity, 9) Suspiciousness, 10) Hallucinations, 11) Unusual thought content, 12) Bizarre behaviour, 13) Self-neglect, 14) Disorientation, 15) Conceptual disorganisation, 16) Blunted affect, 17) Emotional withdrawal, 18) Motor retardation, 19) Tension, 20) Uncooperativeness, 21) Excitement, 22) Distractibility, 23) Motor hyperactivity, 24) Mannerisms and posturing. Items are answered on a 7-point Likert Scale. Every scoring option has a short description of behaviours that must be observed for that particular score. The psychometric properties of the BPRS have often been investigated and BPRS has proven to be a reliable and valid instrument [68, 69]. Internal consistency is good with alphas >0.70.*Overall level of psychological, social and occupational functioning* is measured with the Global Assessment of Functioning (GAF), symptoms and disabilities version (GAF-SD) [70]. GAF is scored on a scale ranging from 0 to 100 with higher scores reflecting fewer symptoms (GAF-S) and handicaps (GAF-D). The GAF-SD has proven to be a reliable and valid measure of psychiatric disturbance in a sample of people with SMI.*Quality of the therapeutic relationship* is measured with the Helping Alliance Scale (HAS) [71]. The HAS was originally developed to measure the quality of the therapeutic relationship from the client’s point of view but an adapted version for the professional’s point of view also exists. Both versions consist of five items concerning the therapeutic relationship. Items are scored on an 11-point visual analogue scale ranging from 0 = not at all to 10 = entirely, with marked 10 mm intervals. Additionally, the client version has a sixth item asking about how patients feel immediately after seeing their MH professional which is answered with unchanged, better or worse. The professional version has two additional open items that ask about positive and negative aspects of the therapeutic relationship. So far, the HAS has not been psychometrically evaluated but has been used in several studies investigating the therapeutic relationship [71–73].*Uptake of the intervention* will be assessed by gathering detailed information about drop-out and non-adherence during the trial.

### Sample size

With regard to the main outcome measure, the power analysis was based on the earlier finding that the proportion of patients engaged in meaningful activities increased by 11.5 % for BPR compared to 0 % for CAU after 1 year [9]. With this expected difference in proportion of change in both conditions, the study will have a power of 80 % (alpha = 0.05, two sided) if complete data from 2 × 90 patients is obtained. Furthermore, with regard to the economic evaluation, SF-12D is used to calculate a preference-based utility index, SF-6D. In the preceding RCT, the SF-12D [58] was not used, but scores on the WHOQOL are available [74]. For patients with rehabilitation goals in the area of societal participation, the differences between BPR and CAU after one year were 1.23 (SD 2.18). Calculating the required power of the study with this parameter, only 60 patients in each condition are needed to achieve 80 % power. Power rises to 95 % with 90 participants in each condition, which is needed for the primary outcome measure. Taking into account an average dropout rate of 20 % and a maximum dropout rate of 25 % after one year follow up, at least 225 respondents with SMI are needed for this trial. The number of patients eligible but not willing to participate will be carefully monitored to support the BIA. A pilot will be conducted for the additional 25 patients with severe and persistent eating disorders who will also participate in this study, since no information is available on the differences in change that can be expected after a year with and without BPR support for this group.

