#### Control group: Care As Usual (CAU)

Patients in the control group will receive CAU conducted according to the guidelines for FACT teams [29, 35, 39, 40] and Dutch RIRCs [31]. These guidelines form a general outline of the philosophy of care for the target groups and the way care is delivered in daily practice. The FACT model, which was developed in The Netherlands [35], contains all elements of the internationally well-known Assertive Community Treatment (ACT) model [41], but FACT differs from ACT in that a FACT team also targets patients who function in a more or less stable manner. These multidisciplinary teams provide medical, psychiatric, social, financial and vocational support, which can be intensified according to the patients’ needs. Detailed information about the Dutch FACT model is described in the English version of the FACT Manual [42].

In the Netherlands, supported housing and supported independent living in the community for patients with SMI is provided by 21 RIRCs. RIRC’s are primarily concerned with patient’s daily activities but also offer some support with regard to participation in society [30, 32]. However, structural support with rehabilitation is often lacking.

In line with the experimental group, participants assigned to the control group will also be offered at least one session every 2 weeks targeting a wish for societal participation, with no predefined maximum or minimum number of sessions that must be completed. Patient and CAU worker plan sessions by agreement and the total number of sessions and duration of their cooperation will be registered.

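### The stated 80% power at 2 × 90 is not justified for the primary endpoint: a net change in the share of active patients is used as if it were the rate of patients who individually increase

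*Protocol article*

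**What the plan says.** The Sample size section states that "the power analysis was based on the earlier finding that the proportion of patients engaged in meaningful activities increased by" a given amount in each arm of the preceding Dutch RCT: 11.5% under BPR and none under CAU. It carries these two figures straight into the calculation ("With this expected difference in proportion of change in both conditions"). The claim drawn from them is that "the study will have a power of 80 % (alpha = 0.05, two sided"), on the condition of 90 evaluable patients in each arm.

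The endpoint is defined elsewhere. Under Primary outcome measures, the first primary outcome is obtained from the employment subscale of the Social Functioning Scale "using a hierarchical index to dichotomise whether or not there is an increase in societal participation at 6 and/or 12 months". Under Primary clinical analyses, "the difference in percentage of patients with increased participation in both groups after 1 year will be compared", with a risk difference and number needed to treat from a regression model.

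The control condition is not passive. Under Control group: Care As Usual, "participants assigned to the control group will also be offered at least one session every 2 weeks targeting a wish for societal participation". No section gives an expected percentage of individual increasers in either arm.

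**The concern.** The planning quantity and the analysed quantity are different things. A change in the proportion engaged is a net figure in which patients who start an activity are offset by patients who stop. The endpoint counts each patient whose own index rises and does not subtract those whose index falls. A net change of 0% therefore says only that gains and losses balanced in the earlier control arm. It does not say that nobody gained.

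Several features of this trial make a control rate of exactly zero hard to defend:

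- every participant has expressed a wish for more participation;
- CAU sessions are aimed at that wish;
- recent employment is a stratification factor, so some patients may have activity to lose as well as to gain;
- the budget impact analysis itself plans to use rates of quitting participation.

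With a hierarchical index, a patient might also move up a level without changing whether he or she counts as engaged. The article does not spell the index out, so that last point is plausible rather than stated.

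The choice of zero matters because the variance of a proportion vanishes there. Any non-zero control rate adds variance, and the same absolute difference becomes harder to detect. This is the only power statement for the main outcome, and the recruitment target of 225 is built on it.

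**Working it through.** **Inputs.** Two-sided α = 0.05 (z = 1.960), power 80% (z = 0.842), rates 11.5% and 0%, and 90 evaluable patients per arm, all from Sample size. The CAU rate of individual increase, *c*, is not in the document and is varied below.

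**Formulas** (two independent proportions, pooled variance under the null; p̄ is the mean of p₁ and p₂, and d = p₁ − p₂):

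- n per arm = [1.960·√(2p̄(1−p̄)) + 0.842·√(p₁(1−p₁)+p₂(1−p₂))]² / d²
- power = Φ{ [d·√n − 1.960·√(2p̄(1−p̄))] / √(p₁(1−p₁)+p₂(1−p₂)) }

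**Step 1: the plan's own figure.** With p₁ = 0.115, p₂ = 0 and p̄ = 0.0575:

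- √(2 × 0.0575 × 0.9425) = 0.3292 and √(0.115 × 0.885) = 0.3190.
- n = (0.6453 + 0.2685)² / 0.115² = 63.1, so 64 per arm. With continuity correction it is 79.6, so 80.
- Power at 90 per arm = Φ{(1.0910 − 0.6453)/0.3190} = Φ(1.397) = 91.9%.

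Other standard variants do not give 90 either. The unpooled formula gives 61, the arcsine formula about 33, and Fisher's exact test between 65 and 70. Power at 90 per arm is 86% with continuity correction and 95% with Fisher's exact test. A value of exactly 90 does appear for 11.5% vs 0.5% with continuity correction, but 0.5% is nowhere in the document.

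**Step 2: a non-zero share of CAU increasers.** Set p₂ = c and p₁ = c + 0.115, with 90 per arm. Example at c = 10%: p̄ = 0.1575, √(2 × 0.1575 × 0.8425) = 0.5152, √(0.215 × 0.785 + 0.10 × 0.90) = 0.5087, so power = Φ{(1.0910 − 1.0097)/0.5087} = Φ(0.160) = 56%.

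| CAU increasers (assumed) | BPR increasers (+11.5 points) | Power at 90 per arm | n per arm for 80% | Difference detectable with 80% power at 90 per arm |
|---|---|---|---|---|
| 0% | 11.5% | 92% | 64 | – |
| 2% | 13.5% | 83% | 84 | – |
| 5% | 16.5% | 71% | 113 | 13.3 points |
| 10% | 21.5% | 56% | 157 | 15.9 points |
| 15% | 26.5% | 48% | 195 | 17.7 points |
| 20% | 31.5% | 42% | 226 | 18.9 points |

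**Step 3: break-even.** Solving for power of 80% at 90 per arm with d = 0.115 gives c ≈ 2.6% (about 1.0% with continuity correction). In a CAU arm of 90, 2.6% is 0.026 × 90 ≈ 2.3 patients.

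**The case against.** A reader might infer from the table that the trial is underpowered, or that 2 × 90 fails to deliver 80%. The document does not support that as a fact, for three reasons.

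- It gives no CAU rate of individual increase. With an 11.5-point difference, 80% is kept up to a CAU rate of about 2.6%.
- On the literal inputs, 90 per arm exceeds the requirement. The gap between 64–80 and 90 is an unexplained margin in the safe direction, perhaps from a small non-zero control rate that the condensed article does not report.
- If net change is the wrong quantity for the control rate, it is also the wrong quantity for the difference. The between-arm difference in individual increasers could be larger or smaller than 11.5 points, and a large enough one restores 80%, as the last column shows. The falling power column is one scenario, not a forecast.

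It can also be said that a null result would not be empty. The trial reports a risk difference and has two further primary measures, the participation ladder and total hours.

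All of this stands, and it limits the conclusion to a claim that is not justified. It does not rescue the claim. The article states the basis of its power calculation, and that basis is a different quantity from the one analysed. This is not a detail left to a fuller document.

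**Conclusion.** The 80% power at 2 × 90 is unsupported for the individual-increase endpoint. It rests on a net change treated as an event rate, and it is not reproduced from its stated inputs, which give about 92%. The true power could lie above or below 80%. It is sensitive to a rate the protocol does not give: with the difference held at 11.5 points, it falls below 80% once more than about 2.6% of CAU patients increase, and is roughly 71% to 42% for CAU rates of 5% to 20%. Those figures rest on the assumed CAU rates, on the assumed 11.5-point difference, and on an unadjusted pooled two-proportion test with complete data from 90 per arm. The mismatch of quantities and the failure to reproduce 80% from 11.5% vs 0% do not depend on the assumed CAU rates.

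**What to change.** Rewrite the first part of the Sample size section for the endpoint that will be analysed. State:

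1. the expected percentage of patients who individually increase in each arm, taken from the preceding RCT if its data can be tabulated that way, and otherwise shown over a CAU range of 5% to 20%;
2. the test and any continuity correction behind the calculation;
3. the resulting power, and the difference detectable with 80% power, at 2 × 90.

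The article shows only that quality-of-life scores from the earlier RCT are at hand for planning, so the tabulation may not be possible. The range can be given in any case.

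The cost is wording and, at most, a re-tabulation of existing data. No extra patients are needed. The downside is that the stated power may become less favourable.
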